## **6. Research Content**

This study was a single-center, randomized, controlled clinical trial protocol planned to include 76 patients with SAP who were randomly divided into two groups in order to assess the efficacy and safety of different SMT-based nurse-led epidural analgesia delivery modalities. In the control group, continuous TEA was used with a combination of nalbuphine 40 mg, ropivacaine 225 mg, lidocaine 0.2 g, and 0.9% saline 6 ml in a total of 50 ml, which was pumped at a rapid duration of 3-5 ml/h. When the patient's VAS-P exceeded 3 points or when the patient was unable to tolerate pain, the pumping of the combined solution was appropriately adjusted upward by 1-2 ml/h. In the experimental group, on the basis of continuous TEA, a pain management nurse led the TEA pain management strategy according to the SMT, reported to the doctor when the VAS-P exceeded 3 points or when the patient was unable to tolerate pain, and injected 5 ml of the combined drug solution intermittently with an intermittent interval time of greater than 2 hours each time, as per the doctor's prescription. Hours. The patient's pain response and feedback were also continuously monitored for timely adjustment of analgesic measures. The primary outcome indicator was VAS-P, and secondary outcome indicators included intra-abdominal pressure(IAP), number of additional interventions(NAI), dosage of combined drugs(DCD) , number of days of epidural placement(NDEP), and 16 adverse events(AE). Outcome indicators included puncture success rate(PSR), length of stay in ICU (ICU-LOS), 28-day mortality rate (28D-MR), and patient satisfaction score for analgesic effect(SAE).

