## 12. Sample size

This study is a randomized controlled trial, and the primary outcome indicator is the VAS-P score. From the literature review, it is known that the mean VAS-P scores after the intervention of similar control group protocols are 1-3, and there is no study similar to the experimental group, and the mean VAS-P scores of the pre-experimental group are 1-2. It is proposed to formulate the standard deviation of the two groups combined  $\sigma = 2.5$ , and it is expected that the pain symptom scores of the experimental group can be decreased by  $\delta = 2$ . Setting a bilaterality of  $\alpha = 0.05$ , the degree of certainty is 90%, and based on the formula of the sample size [Formula 1](#), the sample size is calculated for each group of  $N = 33$  participants. Assuming a 15% dropout rate, a total of 76 participants were needed based on a 1:1 randomization ratio.

*Formula 1:*

$$n = \frac{2(z_{\alpha} + z_{\beta})^2 + \sigma^2}{\delta^2}$$

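### The total of 76 covers about 13% dropout, not the stated 15%; 33 per group and 15% dropout lead to 78 (a minor correction)

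*Protocol*

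**What the plan says.** All the inputs are in Protocol section 12. The test is two-sided at 5% with 90% power ("Setting a bilaterality of $\alpha = 0.05$ , the degree of certainty is 90" per cent). The standard deviation is a planning value: "It is proposed to formulate the standard deviation of the two groups combined $\sigma = 2.5". So is the difference: "it is expected that the pain symptom scores of the experimental group can be decreased by $\delta = 2". From these, "the sample size is calculated for each group of $N = 33$ participants". The dropout step follows: "Assuming a 15% dropout rate, a total of 76 participants were needed based on a 1:1 randomization ratio". The rule used to inflate 33 is not written out. Section 6 repeats the total, with the trial "planned to include 76 patients with SAP who were randomly divided into two groups".

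Formula 1, as it appears in the text, adds sigma squared to the numerator instead of multiplying by it.

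**The concern.** The three figures 33, 15% and 76 are meant to follow from one another, and they do not quite do so. A dropout rate is a share of those randomised, so the evaluable number has to be divided by the share that remains. Multiplying by one plus the rate always gives too few. 

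The evaluable number matters here because losses leave the data set. The dropout criteria in section 11 include epidural placement of less than 3 days, withdrawal of consent, transfer and discharge, and section 24 excludes a patient with two consecutive missing measurements. Section 27 also relies on the sample size calculation as securing the power. If the allowance is too small, the trial should expect to finish slightly under its own target.

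**Working it through.** **Inputs (all from Protocol section 12).** Two-sided alpha 0.05 (z = 1.960); power 90% (z = 1.2816); sigma = 2.5; delta = 2; 33 per group; dropout 15%; total 76 at 1:1, so 38 per group.

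**Step 1. Reproduce the 33.** The usual formula for two means is n = 2(z_{alpha/2} + z_beta)² × sigma² / delta².

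2 × (1.960 + 1.2816)² × 6.25 / 4 = 32.84, rounded up to 33. The stated figure reproduces.

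**Step 2. Formula 1 as it appears.** With sigma² added in the numerator: (2 × (1.960 + 1.2816)² + 6.25) / 4 = 6.8, so 7 per group. The stated 33 therefore came from the product form with the two-sided z, and the plus sign played no part in it.

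**Step 3. Reproduce the 76.**

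- 33 × (1 + 0.15) = 37.95, so 38 per group and 76 in total. This matches the stated total exactly.
- 33 / (1 − 0.15) = 38.82, so 39 per group and 78 in total.
- Starting from the unrounded 32.84 does not change this: 32.84 / 0.85 = 38.6, again 39.

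**Step 4. What 76 provides.**

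- Expected evaluable patients at 15% loss: 38 × 0.85 = 32.3 per group, which is 0.7 below 33.
- Largest dropout that still leaves 33 of 38: 1 − 33/38 = 13.2%.

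**Step 5. Power at delta/sigma = 2/2.5 = 0.8.** For the normal approximation, power = Phi(0.8 × √(n/2) − 1.960). At n = 32.3 this is Phi(3.215 − 1.960) = 89.5%; at n = 33 it is Phi(3.250 − 1.960) = 90.1%. The last column uses the noncentral t distribution.

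| Evaluable per group | Normal approximation | t-test |
|---|---|---|
| 32 | 89.3% | 88.3% |
| 32.3 (expected from 38) | 89.5% | 88.6% |
| 33 (the stated target) | 90.1% | 89.3% |
| 33.15 (expected from 39) | 90.3% | 89.4% |
| 34 | 91.0% | 90.2% |

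The dropout step costs 90.1 − 89.5 = 0.6 points on the Protocol's own method and 89.3 − 88.6 = 0.7 points by t-test.

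**Step 6. Chance of keeping 33.** If each patient drops out independently with probability 15%, a group of 38 keeps at least 33 with probability 48.5%, and both groups do so with probability 0.485² = 24%. With 39 per group the figures are 63.3% and 0.633² = 40%.

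**The case against.** The case for leaving this alone is that nothing of consequence follows. The gap is 2 patients in 76 (2.6%). Both sigma and delta are planning values, and the uncertainty in them can be expected to outweigh a change of about 0.6 points of power. The 76 is also traceable: adding 15% to 33 and doubling gives it exactly, and section 6 agrees. All of that stands, and it is why the point is minor. It does not make 76 the number that allows for a 15% dropout rate.

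A reader might go further, in three ways that the Protocol does not support.

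- *That the design fails to deliver its 90% power.* Setting 88.3% or 88.6% against the stated 90% mixes two methods. The stated 90% belongs to the normal approximation. By t-test, 33 per group already gives only 89.3%, and the arithmetically correct 39 per group gives 89.4% at 15% dropout, so it would miss 90% as well. Using the normal approximation is common practice and is not an error.
- *That a shortfall is certain.* Only the expected number falls below 33; each group has close to an even chance of keeping 33 or more. The 24% for both groups looks alarming only without its comparator of 40% at 39 per group.
- *That the sample size was calculated with a wrong formula.* The 33 agrees with the product form, so the plus sign did not enter the calculation. It may be a misread symbol in the conversion from PDF.

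**Conclusion.** The dropout allowance is misstated. From 33 per group and 15% dropout, the total is 78; the stated 76 covers about 13.2%. At 15% dropout the expected shortfall is 0.7 evaluable patients per group and about 0.6 points of power, leaving about 89.5% on the Protocol's own approximation (about 88.6% by t-test). This is a minor correction of a stated figure, and it raises no doubt about whether the trial can meet its aim.

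The conclusion rests on reading 15% as a share of those randomised, with equal loss in both groups, and on the Protocol's delta and sigma. The power figures are for a simple comparison of two means, as in Formula 1. That 76 came from multiplying by 1.15 is inferred from the exact match; the shortfall against 33 does not depend on that inference.

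The Formula 1 point is secondary and conditional on the plus sign being in the source.

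**What to change.** In section 12, do one of the following:

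- keep 76 and state that it covers about 13% dropout, or that it gives about 89% power at 15% dropout; or
- give 39 per group, 78 in total, as the number that follows from 33 and 15%, and change the 76 in section 6 to match.

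In the same edit, check Formula 1 against the source file. If the plus sign is there, print n = 2(z_{alpha/2} + z_beta)² × sigma² / delta², which is the form that gives 33. Writing alpha/2 also makes the two-sided z explicit.

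The cost is one sentence and, if needed, one formula. The first option makes the stated allowance or power slightly less favourable; the second adds two patients.

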## 13. Randomization

The study participants were evenly divided into the control group and experimental group using random numbers generated with SPSS 29.0 software. Randomization will be performed by an unblinded study coordinator who does not perform any intervention or outcome assessments. Research staff, with no clinical involvement in the trial, will be responsible for keeping the random allocation list and preparing sealed, opaque sequentially numbered envelopes, each containing a random number denoting the allocated treatment. Participants meeting the inclusion criteria will randomly select a sealed envelope containing the intervention protocol.

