## 14. Blinding

Because this is an interventional study, pain management nurses will not be aware of the specific grouping of patients until after they begin to implement the intervention, but they will not be involved in other parts of the study. Although there are measures that can be taken to try to keep patients blinded to subgroups, there are still difficulties in avoiding exposure altogether. For this reason, data collectors and data analysts will remain blinded to the specific intervention protocols, and independent persons who are not aware of the specific intervention protocols will be responsible for data collection and analysis, thus ensuring that data collectors and statistical

analysts are blinded to the treatment assignment and minimizing potential bias in data processing and analysis.

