## **19.Primary outcome measure**

Visual Assessment Scale-Pain (VAS-P): which consists of a 100-mm straight line, with one end indicating “no pain at all” and the other end indicating “the most severe pain imaginable”, with the patient marking the corresponding position on the line to represent his/her pain level. Patients marked the corresponding position on the line to represent their pain level. The data were collected by the data collectors at the specified time points (0h, 1h, 6h, 12h, 24h, 48h, 72h). Among them, 0h was before epidural placement, and the other times were 1h, 6h, 12h, 24h, 48h and 72h after epidural placement.

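### Section 13 has the participant draw an envelope that may show the arm to the person who scores the primary outcome, and it contradicts itself on what the envelope holds

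*Protocol*

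**What the plan says.** **Allocation (Protocol, section 13).** Three statements bear on the point:
- The person responsible: "Randomization will be performed by an unblinded study coordinator who does not perform any intervention or outcome assessments".
- The container and its content: "sealed, opaque sequentially numbered envelopes, each containing a random number denoting the allocated treatment".
- The participant's part: "Participants meeting the inclusion criteria will randomly select a sealed envelope containing the intervention protocol".

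**Blinding (section 14).** On patients the protocol says "Although there are measures that can be taken to try to keep patients blinded to subgroups, there are still difficulties in avoiding exposure altogether". Its answer follows directly: "For this reason, data collectors and data analysts will remain blinded to the specific intervention protocols".

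**Who scores (sections 19, 20 and 22).** The primary outcome is self-rated: "Patients marked the corresponding position on the line to represent their pain level". Satisfaction with analgesia is also the patient's own score, on a 0-10 scale. The number of additional interventions (NAI) counts responses to a VAS-P above 3 or to pain the patient cannot tolerate, so it too depends on what the patient reports.

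**Treatment (sections 6 and 17).** Both arms are planned to have the same drug mixture by continuous thoracic epidural infusion, with the same trigger for extra intervention. After the trigger, the control arm has its infusion rate raised and the experimental arm has an epidural injection.

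**The concern.** When the patient is the rater, the patient's knowledge of the arm is the exposure that matters most. Someone who knows they are in the new, individualised regimen may mark less pain, report intolerable pain at a different threshold, or give a higher satisfaction score. This expectation would enter VAS-P, NAI and satisfaction together. Section 14 responds by blinding those who collect and analyse the data, but they take over the mark the patient has already made, so their blinding leaves the bias in place.

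Section 14 treats some patient exposure as hard to avoid. Exposure at the draw is a different matter. It can be avoided by procedure, and it would come before treatment gives the patient any clue.

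**Working it through.** The point rests on reading sections against each other. The arithmetic in step 5 is only an illustration.

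**1. What the envelope holds and who handles it.** Within section 13:

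| Question | One statement | Other statement |
|---|---|---|
| Content | a random number standing for the treatment | the intervention protocol |
| Order | sequentially numbered | picked at random |
| Actor | unblinded coordinator | participant |
| Who opens or reads it | not stated | not stated |

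A number alone need not reveal the arm. An intervention protocol would, if the patient sees it. The section therefore permits disclosure without establishing it.

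**2. Could the patient tell the arm anyway?** Sections 6 and 17 plan the same continuous infusion in both arms and the same trigger, so drug delivery alone would not show the arm before the first extra intervention. Nursing care might. Sections 6 and 17 attach the nurse-led strategy based on Symptom Management Theory (SMT) to the experimental arm, and hypothesis 3 in section 7 credits that programme for higher satisfaction. Section 8, however, describes the strategy as covering both regimens, and section 20 has pain management nurses giving the extra interventions in both groups. The protocol does not settle whether this care differs between arms.

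**3. Which scores could be exposed?** Every score from 1h to 72h follows allocation. For the 0h score the sections disagree:
- Section 9 lists randomization as step 1, pain assessment as step 2 and catheter placement as step 3. The schedule in section 35 also puts allocation before 0h. On this order the 0h score follows the draw.
- Section 16 collects baseline data before enrolment, including the pain score before placement, and section 19 defines 0h as before placement. On this order the 0h score precedes the draw.

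**4. The plan's own figure.** Inputs from section 12: SD 2.5, difference 2, two-sided alpha 0.05, power 90%. With the usual formula, n = 2(z_α/2 + z_β)²σ²/δ² = 2 × (1.960 + 1.282)² × 6.25 / 4 = 32.84, so 33 per group. The stated 33 is reproduced. (Formula 1 as printed has a plus sign where this product is needed; that is a separate matter.)

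**5. Sensitivity to unblinding in general.** Assumption, with no source in the protocol: knowing the arm shifts self-scored VAS-P by b points between arms, in the units of section 12, and there is no true effect. For a single two-sample t-test with 33 evaluable per arm:
- standard error = 2.5 × √(2/33) = 0.615
- degrees of freedom = 64, critical value 1.998
- noncentrality = b / 0.615

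| Assumed shift b | Noncentrality | Rejection rate | Share of planned difference of 2 |
|---|---|---|---|
| 0 | 0 | 5.0% | 0 |
| 0.25 | 0.41 | 6.9% | 1/8 |
| 0.5 | 0.81 | 12.6% | 1/4 |
| 1.0 | 1.62 | 36.0% | 1/2 |

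The normal approximation gives 6.9%, 12.8% and 36.9% for the three shifts, so the result hardly depends on that choice.

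**The case against.** **Disclosure is not written down.** A reader might infer that every patient learns the arm at the draw. The document does not support that. The envelopes are opaque and sealed, one sentence says they hold only a number, a coordinator performs the randomization, and nothing says the participant opens or reads anything. This stands, and the point is limited to what the wording permits.

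**No promise is broken.** Section 14 concedes that patient exposure cannot be wholly avoided and commits only to blinding collectors and analysts. How far to pursue partial patient blinding is largely a design choice. This also stands. The defect is avoidable early exposure of a self-rater, not failure to keep a stated blind.

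**The arms may differ from the start.** It is tempting to say that they are treated alike until the first extra intervention. Only the planned infusion and the trigger are shown to be alike. If SMT-based nursing is given in one arm only, patients might infer the arm from their care even with a perfect allocation procedure.

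**The 0h score.** A reader might take it that baseline is contaminated too. Section 16 points against this, and the order has to be reconciled before either reading is safe.

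**The rejection rates.** They use an assumed shift and a single t-test, whereas section 24 plans repeated-measures ANOVA over seven time points. They also charge the whole effect of unblinding to the envelope, although patients may infer the arm later from an injection. The objection is right that they do not measure the benefit of changing section 13.

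None of this resolves the contradiction in section 13 or supplies a safeguard against the patient seeing the content.

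**Conclusion.** The point holds in a limited form. Section 13 gives two incompatible accounts of the envelope's content, does not say who opens it, and on one of those accounts can show the allocated arm to the patient who rates the primary outcome and satisfaction and whose report drives NAI. Section 14's safeguards do not reach a self-rated score.

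The firm part is the contradiction and the missing safeguard, which need no assumption. The bias is conditional on the patient seeing the arm and on that knowledge changing the score. Its size is unknown; 6.9% to 36.0% shows only how sensitive a trial of this size is to an assumed shift of 0.25 to 1 point. What belongs to the envelope is the added exposure before the first extra intervention, and throughout in patients who never need one. That part cannot be estimated from the protocol.

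This is a worthwhile, inexpensive improvement to the allocation procedure. It is not evidence that the trial's comparison is invalid.

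**What to change.** **Section 13.** State one content for the envelope and delete the participant's draw. The unblinded coordinator, who is already in the plan, takes the next numbered envelope and opens it away from the patient after the 0h VAS-P has been recorded. The coordinator passes the assignment only to the staff who must prescribe and deliver the intervention, at the time section 14 allows. Telling the nurse alone would not suffice, because section 6 has the injection given on a doctor's prescription.

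**Section 14.** State that at consent patients are informed of both schedules and their risks, including the possible injection, but are not told their assigned arm. This keeps the full information that section 11 requires.

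**Consistency.** Bring sections 9, 16 and 35 into line on whether the 0h score precedes allocation. Reconcile sections 6, 7 and 17 with sections 8 and 20 on whether SMT-based nursing is given in one arm or both.

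**Cost.** A protocol amendment and matching consent text; no new staff and no change to sample size. Blinding stays partial, because patients may still infer the arm from nurse-led care or once an injection is given.

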## 14. Blinding

Because this is an interventional study, pain management nurses will not be aware of the specific grouping of patients until after they begin to implement the intervention, but they will not be involved in other parts of the study. Although there are measures that can be taken to try to keep patients blinded to subgroups, there are still difficulties in avoiding exposure altogether. For this reason, data collectors and data analysts will remain blinded to the specific intervention protocols, and independent persons who are not aware of the specific intervention protocols will be responsible for data collection and analysis, thus ensuring that data collectors and statistical

analysts are blinded to the treatment assignment and minimizing potential bias in data processing and analysis.

### **15.Trial Equipment**

The test equipment included a micro syringe pump, drugs (nalbuphine 20mg/2ml, ropivacaine 75mg/10ml, lidocaine 0.1g/5ml) and an epidural puncture placement kit. The micro syringe pump is used to accurately control the pumping rate and dosage of medication to ensure that the medication is pumped consistently and uniformly to maintain a stable analgesic effect. It is also possible to regulate the exact dose to be injected at one time. Nalbuphine acts as a potent analgesic by agonizing the  $\kappa$  opioid receptor; Ropivacaine is an amide-type intermediate local anesthetic that provides local anesthesia and analgesia; Lidocaine is an amino-amide-type local anesthetic that provides analgesia and anti-inflammatory effects. The Epidural Puncture Placement Kit contains a puncture needle, catheter, etc., which is used to safely place the catheter into the epidural space to ensure accurate drug pumping.

### **16.Data collection process**

After patients were admitted to the ICU, eligible study subjects were screened according to the inclusion and exclusion criteria. Before enrollment, the following baseline data were collected: patients' general information: including age, gender, and time of admission; important clinical and diagnostic information: including etiology of onset, time from onset to admission, time from onset to admission to the ICU, time from onset to TEA, history of previous chronic diseases, related complications, type of SAP pathology, CTSI score, Ranson score, APACHE-II score and major interventions during hospitalization; and pain score and intra-abdominal pressure before epidural placement. These baseline data cover the basic characteristics, clinical status and pain of the patients and provide a comprehensive reference for subsequent assessment of pain management outcomes.

### **17.Study interventions**

Control group: Continuous TEA using a drug combination of: nalbuphine 40 mg + ropivacaine 225 mg + lidocaine 0.2 g + 0.9% saline 6 ml in a total volume of 50 ml at an infusion rate of 3-5 ml/h. When the patient's VAS-P exceeded a score of 3 or the pain was intolerable, upward adjustment of the pumped medication was made by 1-2 ml/h. and the number of additional interventions was recorded.

Experimental group : On the basis of continuous TEA, the pain management nurse led the TEA management strategy based on STM, and when the patient's VAS-P exceeded a score of 3 or pain was intolerable, an epidural injection of 5 ml of the combined drug solution was immediately administered, and the number of additional interventions was recorded. The duration of each interval was greater than 2 hours, and the patient's pain response and feedback were continuously monitored so that analgesic measures could be adjusted in a timely manner.

